## Abstract

**Background:**

Anastomotic leakage is the most important surgical complication following esophagectomy. A major cause of leakage is ischemia of the gastric tube that is used for reconstruction of the gastrointestinal tract. Generalized cardiovascular disease, expressed by calcifications of the aorta and celiac axis stenosis on a pre-operative CT scan, is associated with an increased risk of anastomotic leakage. Laparoscopic ischemic conditioning (ISCON) aims to redistribute blood flow and increase perfusion at the anastomotic site by occluding the left gastric, left gastroepiploic and short gastric arteries prior to esophagectomy. This study aims to assess the safety and feasibility of laparoscopic ISCON in selected patients with esophageal cancer and concomitant arterial calcifications.

**Methods:**

In this prospective single-arm safety and feasibility trial based upon the IDEAL recommendations for surgical innovation, a total of 20 patients will be included recruited in 2 European high-volume centers for esophageal cancer surgery. Patients with resectable esophageal carcinoma (cT1-4a, N0–3, M0) with “major calcifications” of the thoracic aorta accordingly to the Uniform Calcification Score (UCS) or a stenosis of the celiac axis accordingly to the modified North American Symptomatic Carotid Endarterectomy Trial (NASCET) score on preoperative CT scan, who are planned to undergo esophagectomy are eligible for inclusion. The primary outcome variables are complications grade 2 and higher (Clavien-Dindo classification) occurring during or after laparoscopic ISCON and before esophagectomy. Secondary outcomes include intra- and postoperative complications of esophagectomy and the induction of angiogenesis by biomarkers of microcirculation and redistribution of blood flow by measurement of indocyanine green (ICG) fluorescence angiography.

**Discussion:**

We hypothesize that in selected patients with impaired vascularization of the gastric tube, laparoscopic ISCON is feasible and can be safely performed 12–18 days prior to esophagectomy. Depending on the results, a randomized controlled trial will be needed to investigate whether ISCON leads to a lower percentage and less severe course of anastomotic leakage in selected patients.

**Trial registration:**

Clinicaltrials.gov, NCT03896399. Registered 4 January 2019.

**Supplementary Information:**

The online version contains supplementary material available at 10.1186/s12885-022-09231-x.

## Background

Transthoracic esophagectomy with 2-field lymphadenectomy is the standard of surgical care for patients with esophageal cancer [1]. The reconstruction of choice is a gastric tube with intrathoracic (Ivor-Lewis) or cervical esophagogastrostomy (McKeown). This gastric tube is perfused only by the right gastroepiploic artery, as all other gastric arteries are ligated during gastric mobilization. This is associated with severe change of microcirculation in the gastric tube, reducing gastric perfusion up to 50% [2–5]. Reduced blood flow may lead to impaired healing of the anastomosis and could result in anastomotic leakage. Anastomotic leakage occurs in 15–30% of patients after esophagectomy [6]. It is considered the most important complication after esophagectomy, increasing postoperative morbidity and mortality. Anastomotic leakage has a multifactorial etiology. Some risk factors have been identified, such as severe comorbidity, diabetes mellitus, smoking status, radiation field and cervical anastomosis [7, 8].

Another important risk factor is the vascular status which can be inferred from calcification in the thoracic aorta, defined by the uniform calcification score (UCS). The UCS is calculated on diagnostic CT scans by scoring the presence of arterial calcification in the thoracic aorta based on a visual grading system. In addition, the presence of a local stenosis of the celiac trunk is also associated with an increased risk of anastomotic leakage [9]. This stenosis is defined by the modified North American Symptomatic Carotid Endarterectomy Trial score (modified NASCET score). Higher percentages of anastomotic leakage (33–37%) were observed in patients with calcifications compared to patients without calcifications, who had lower incidences of leakage (9–19%) [10–12].

The higher prevalence of anastomotic leakage in these patients are hypothesized to be the result of a reduced micro or macro perfusion of the gastric tube [2–4, 13]. Anastomotic leakage percentages might be reduced by ischemic conditioning (ISCON) of the gastric tube. ISCON aims to increase perfusion at the anastomotic site by redistribution of the gastric blood flow [14]. This is achieved by occluding all of the gastric arteries except the right gastric and right gastroepiploic artery during a separate intervention, days or weeks prior to esophagectomy.

To date, several studies reported ISCON to be safe in esophageal surgery and its possible efficacy in decreasing anastomotic leakage [15, 16]. However, all studies were retrospective and performed in unselected patients. Therefore, the current prospective safety and feasibility trial aims to investigate the feasibility and safety of performing laparoscopic ISCON for esophageal cancer in patients at high-risk for anastomotic leakage, as based upon their vascular status on pre-operative CT scans (defined by the UCS of the thoracic aorta and modified NASCET score of the celiac axis). The hypothesis of this study is that in these selected patients with an increased risk of vascular impairment of the gastric tube, laparoscopic ISCON is feasible and can be safely performed prior to esophagectomy.

## Methods/design

### Design

This study is designed as a prospective single-arm safety and feasibility trial performed at the University Medical Center Utrecht and the University Hospital of Cologne.

### Ethical consideration

The study protocol was approved by the Medical Ethical Committees of the University Medical Center Utrecht (reference number NL67819.041.18) and the University of Cologne (reference number 18–299). The trial was prospectively registered at clinicaltrials.gov.

### Patient population

All patients with a resectable esophageal carcinoma (cT1-4aN0-3 M0) scheduled for an esophagectomy are eligible for screening for inclusion in the study. Accordingly to policies in the Netherlands and Germany, included patients undergo neoadjuvant chemo(radio) therapy followed by laparoscopic ISCON and subsequent esophagectomy. An exception will be made for patients with early esophageal cancer (cT1-2N0M0) and patients who are not fit enough for neoadjuvant treatment, they will bypass neoadjuvant treatment and undergo primary ISCON followed by esophagectomy. Detailed inclusion and exclusion criteria are listed below.

Inclusion criteria:Histologically proven adenocarcinoma or squamous cell carcinoma of the esophagus or gastroesophageal junctionPlanned to undergo transthoracic esophagectomy or transhiatal esophagectomyPreoperative CT-scanArterial calcifications: “major calcifications” of the thoracic aorta according to the (UCS) or a stenosis of the celiac axis according to the modified NASCET scoreASA classification I-IIIEuropean Clinical Oncology Group (ECOG) performance status of 0–2Age > 17Written informed consent

Exclusion criteria:Not able to undergo study treatmentPresence of metastatic disease

### UCS and NASCET score

Preoperative staging examinations of all patients are routinely performed on CT scanners with 64 detector rows or more. A slice thickness of maximum 3.0 mm is used. Two clinicians (of whom at least one is a radiologist) will independently score the calcifications on the preoperative CT scans of the thoracic aorta (UCS score) and the celiac axis (modified NASCET score). Any disagreements will be solved based on discussion. The UCS will be used in order to consistently score CT images on arterial calcification at the thoracic aorta (heart – celiac axis). Scores of 0, 1 or 2 will be assigned, corresponding with absent, minor or major calcifications, respectively (see Table 1). Stenosis of the celiac axis will be evaluated by using multiplane reconstructions. Accordingly to the NASCET score, the diameters of the normal (a) and narrowest (b) lumen of the celiac axis will be measured. The percent stenosis (s) will be calculated using the following formula: s = (a-b)/a × 100.

**Table 1 Tab1:**
[figure not shown]
Uniform Calcification Score: Definitions used to visually grade arterial calcification on preoperative CT images. MCSD: maximum cross-sectional diameter

*****these anatomical locations are secondary outcome measures

### Laparoscopic ISCON

The first operation aims to partially devascularize the stomach by laparoscopic clipping of the left gastric artery, reached through the hepatogastric ligament at the lesser curvature. Furthermore, transection (with the harmonic scalpel or comparable instrument) of the short gastric vessels including the left gastroepiploic artery is performed. This operation will be kept as minimalistic as possible. Vascularization of the right gastric artery and the right gastroepiploic artery along the greater curvature will remain preserved. No lymph node dissection or gastric tube formation will be performed.

### Postoperative management ISCON

Patients are allowed to drink liquids, soup and supplemental nutrition drinks (high energy, high protein oral nutritional supplements) on postoperative day 0. All patients will have a form of liquid or solid enteral nutrition between ISCON and esophagectomy. Patients will be eligible for discharge on postoperative day 3, depending on the clinical course. A dietician will be consulted to ensure that the patient is optimized in terms of nutrition between ISCON and esophagectomy. All patients will receive a mandatory outpatient clinic standard follow-up appointment on postoperative day 6–8, unless they are still admitted at the hospital. Patients will be re-admitted 0–1 day before esophagectomy.

### Esophagectomy

Esophagectomy will be performed after an interval of 12–18 days after ISCON. If a gastroparesis is suspected, a nasogastric tube will be placed before anaesthesia to avoid aspiration. Esophagectomy will consist of a transthoracic esophagectomy with intrathoracic or cervical anastomosis or a transhiatal esophagectomy with cervical anastomosis. In the University Hospital of Cologne, an intrathoracic anastomosis will be created in all patients except for those with a tumor localized in the cervical compartment. In the University Medical Center Utrecht, a cervical anastomosis will be created for proximal and mid esophageal tumors while an intrathoracic anastomosis will be created for distal esophageal tumors. Alternatively, instead of a transthoracic esophagectomy, a transhiatal esophagectomy can be performed in patients with increased comorbidity.

The esophagectomy includes laparoscopic gastric mobilization, abdominal lymph node dissection, intrathoracic lymph node dissection (for transthoracic esophagectomies), esophagectomy and intrathoracic or cervical anastomosis. The abdominal phase will be performed as a minimally invasive procedure, the thoracic procedure can be performed by an open or a (robot assisted) thoracoscopic approach.

If, for any reason, it is not possible to perform the second operation within 12–18 days, it will be attempted to perform the second operation as soon as possible (i.e. within 30 days) based on the discretion of the surgeon who performed the first operation.

### Translational program

To assess the effect of laparoscopic ISCON on macro- and microcirculation, a translational program is included in the study. This program consists of two parts: measurements of macro- and microcirculation. This will be investigated by means of blood samples (cytokine profile), biopsies (vascularity) and ICG fluorescence angiography. Blood samples will be collected before ISCON and esophagectomy and will be screened on biomarkers. The presence and the level of biomarkers will be compared in the blood samples before and after ISCON to detect potential changes. Biopsies will be taken via gastroscopy preoperatively to ISCON as well as esophagectomy, either within 24 h before surgery or immediately after anesthesia. Three biopsies will be taken from the gastric fundus since the anastomosis will likely be located somewhere in the fundus. In order to identify the fundus, the endoscopy will be performed right after the laparoscopic camera is inserted so that the table surgeon is able to point out the fundus. Finally, if a stapler is used for performance of the anastomosis, the gastric anastomotic donut will be collected and if the anastomosis is hand-sewn, the tip of the gastric tube will be collected to for further pathological analysis and to detect morphological changes of the microvasculature. ICG will be performed during ISCON, before and after the occlusion of the gastric arteries and during esophagectomy, before the creation of the gastric conduit and optionally before the creation of the intrathoracic anastomosis. The ICG procedure is standardized and included in the protocol as described in Supplementary 1. The goal is to quantify the effect of laparoscopic ISCON on gastric perfusion which is described in Supplementary 2. During ICG, the camera keeps the gastric fundus in view. If ICG is also performed for the anastomosis, the camera keeps the gastric conduit in view. The different time points of the translational program are summarized in Table 2.

**Table 2 Tab2:** Summary of time points of the translational program. h = hour

	ICG fluorescence	Biomarkers
< 24 h to start of ISCON		Biopsies of anastomotic site + peripheral blood (10 ml EDTA)
ISCON: before occlusion of arteries	X	
ISCON: 10 min after occlusion of arteries	X	
< 24 h to start of esophagectomy		Biopsies of anastomotic site + peripheral blood (10 ml EDTA)
Esophagectomy: before formation of gastric tube	X	
Optional: esophagectomy: before formation of intrathoracic anastomosis	(X)	
Esophagectomy: after completion of anastomosis		Gastric anastomotic donut or tip of gastric tube

### Primary outcome

Complications are defined according to the Esophageal Complications Consensus Group (ECCG) and graded according to the Clavien Dindo Classification [1, 17]. The primary outcome measure is the percentage of complications grade ≥ 2 occurring during or after ISCON and before esophagectomy.

### Secondary outcomes

The main secondary outcome measures include all grade 1 complications occurring during or after ISCON and before esophagectomy according to the Clavien Dindo Classification. Intraoperative outcomes will be scored during both surgeries including the presence of adhesions, intraoperative complications and the vascularisation of the stomach (based on the color of the tissue). Furthermore, for ISCON, the duration of the procedure, blood loss, oral intake, weight and day of discharge will be collected. Lastly, 30 day mortality, anastomotic leakage of any grade and all other postoperative complications grade ≥ 3b will be collected after esophagectomy.

### Translational outcomes

Secondary outcomes regarding the translational program are induction of angiogenesis by biomarkers of microcirculation, redistribution of blood flow by measurement of indocyanine green (ICG) fluorescence angiography. Serum levels of several proangiogenic cytokines (VEGF, IL-8, IL-6, TNF-α and Ang-2) will be determined in peripheral blood samples by ELISA [18]. The obtained biopsies and gastric donut samples/tip of the gastric conduit will be collected from the endoscopy unit or the operation theatre and will be fixed in formaldehyde. Paraffin embedded sections (10 μm) will be stained by immunohistochemistry against CD31 (vessel density) or smooth-muscle-actin positive pericytes to detect morphological changes of the microvasculature. The strength of the ICG will be scored on videos that are recorded during the operation in 2 fashions, subjectively and objectively.

### Data collection

All data will be collected and stored in an electronic Clinical Research Form application called OpenClinica. The coordinating investigators will oversee the overall data collection process. OpenClinica generates a subject number for each patient and securely stores all entered research data in a pseudonymized fashion. A code file that links subjects numbers to individual patients will be securely stored in each center, and will only be accessible to the local study coordinators. Collected baseline data (age, gender, body mass index, comorbidities) and treatment details (neoadjuvant therapy, surgical techniques, postoperative complications, mortality) will be prospectively entered in a case report form with built-in validation checks. Painscores according to numeric rating scale 0-10 will be collected at postoperative day 1-3 after ISCON. In addition, radiological findings at the coronary arteries, supra-aortic arteries and celiac axis (UCS) will be scored. Patient-reported outcome measures (PROMs) will be collected prior to both surgeries by asking patients to complete the questionnaires (EORTC QLQ-C30 and QLQ-OG25).

### Sample size

This is a prospective single arm safety and feasibility trial, classified as a “stage 2a Development” study according to the IDEAL recommendations for surgical innovation [19]. Based upon these recommendations, a total of 20 subjects will be included and no formal sample size calculations are performed (10 patients per centre).

### Statistical analyses

Statistical analyses in this study are primarily based on descriptive means. Categorical data will be summarized as frequencies. Normally distributed continuous data will be summarized as means with corresponding standard deviations. Non-normally distributed continuous data will be summarized as medians with corresponding interquartile ranges. Repeated outcomes at various time points (such as translational outcomes and PROMS) will be presented descriptively and tested as paired measurements analysis will be performed with SPSS software (IBM).

### Data safety monitoring board & monitoring

This study is classified as a medium risk study. Monitoring will be performed in both centers by an external independent Contract Research Organization according to the Study Monitoring Plan. Based upon advice of the Data Safety Monitoring Board (DSMB) of the UMC Utrecht, a DSMB will not be assigned. Instead of a DSMB, an independent Medical Safety Officer -a Professor in Gastroenterology- was assigned to perform ongoing safety surveillance together with the researchers. After the first 5 patients underwent esophagectomy, all serious adverse events (SAEs) will be evaluated with the Medical Safety Officer. After the first 10 patients underwent both surgeries, an interim analysis will be performed which is described in detail below. All SAEs will be reported by the sponsor to the ethical committee and to the Medical Safety Officer.

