### Interim analysis

An interim analysis will be performed after hospital discharge (after esophagectomy) of the first 10 patients included in the study. The stopping rules are the occurrence of one of the following:> 40% postoperative complication of gastric perforation requiring re-intervention, during or after laparoscopic ISCON and before esophagectomy.> 40% patients having an aspiration pneumonia after laparoscopic ISCON, resulting in a prolonged hospital stay.> 40% patients not able to undergo the planned esophagectomy within 30 days after laparoscopic ISCON, due to complications specifically attributed to laparoscopic ISCON.

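### The interim look is defined on two different sets of ten patients, and both triggers require esophagectomy although the third stopping rule counts patients unable to have it within 30 days

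*Protocol article*

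**What the plan says.** The protocol article defines the interim look twice.

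- *Data safety monitoring board & monitoring*: "After the first 10 patients underwent both surgeries, an interim analysis will be performed which is described in detail below".
- *Interim analysis*: "An interim analysis will be performed after hospital discharge (after esophagectomy) of the first 10 patients included in the study".

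The second section then lists three stopping rules, each with a threshold of more than 40%:

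1. Rule 1 concerns more than "40% postoperative complication of gastric perforation requiring re-intervention, during or after laparoscopic ISCON and before esophagectomy".
2. Rule 2 concerns aspiration pneumonia after ISCON that lengthens the hospital stay. Its wording does not end the period at esophagectomy.
3. Rule 3 concerns more than "40% patients not able to undergo the planned esophagectomy within 30 days after laparoscopic ISCON, due to complications specifically attributed to laparoscopic ISCON".

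The monitoring section has an earlier review that is also tied to the second operation: "After the first 5 patients underwent esophagectomy, all serious adverse events (SAEs) will be evaluated with the Medical Safety Officer". The same section replaces a DSMB with a Medical Safety Officer, "assigned to perform ongoing safety surveillance together with the researchers", who also receives all SAE reports.

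If the planned interval of 12–18 days cannot be kept, the *Esophagectomy* section says that "it will be attempted to perform the second operation as soon as possible (i.e. within 30 days"). The *Sample size* section fixes the total at 20 patients without a formal calculation.

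**The concern.** One section counts patients who completed both operations; the other counts patients included. The two sets are the same only if each of the first 10 included patients has esophagectomy, and has it before any later patient does.

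In both versions esophagectomy is part of the trigger, while rule 3 counts the failure to reach esophagectomy in time. The article does not say how a patient who never has the second operation enters the trigger or the denominator. The effect depends on which section is followed:

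- **Monitoring section.** Never-operated patients are excluded by definition. Rule 3 can then see only operations done after day 30. Rules 1 and 2 lose a patient only where the perforation or pneumonia permanently prevents surgery.
- **Interim analysis section, read literally.** A never-operated patient has no discharge after esophagectomy, so the condition for holding the look is not met.

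At stake are the only numerical stopping rules in a safety and feasibility trial. In either case the error is in the unsafe direction: the more patients ISCON keeps from surgery, the less rule 3 sees or the later the look comes.

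**Working it through.** The article gives no computed figure for the interim look, so there is none to reproduce. The steps below show what the two definitions do to rule 3.

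**Inputs from the protocol article.** Ten patients at the look; a threshold of more than 40%; 20 patients in total.

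**Inputs that are assumptions.** The documents give no rate for rule-3 events. Let q be the true probability of a rule-3 event and f the share of rule-3 patients who are never operated; the rest are operated after day 30. Patients are taken as independent, and the order in which they complete surgery is ignored.

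**Step 1, threshold.** 4/10 = 40% does not exceed 40%, and 5/10 does. Rule 3 therefore needs at least 5 of 10.

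**Step 2, first 10 with everyone kept.** P(rule met) = P(X ≥ 5), X ~ Binomial(10, q). This does not depend on f.

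**Step 3, first 10 completers.** Never-operated patients, a fraction qf, are removed. Among completers the visible rule-3 rate is q(1−f)/(1−qf). At q = 0.5 and f = 0.5 this is 0.25/0.75 = 0.333. At f = 1 it is 0. Then P(rule met) = P(X ≥ 5) at that rate.

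| q (assumed) | First 10, all kept | 10 completers, f = 0.5 | 10 completers, f = 1 |
|---|---|---|---|
| 0.2 | 0.033 | 0.003 | 0 |
| 0.3 | 0.150 | 0.020 | 0 |
| 0.4 | 0.367 | 0.078 | 0 |
| 0.5 | 0.623 | 0.213 | 0 |
| 0.6 | 0.834 | 0.440 | 0 |

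At f = 0, where every rule-3 patient is eventually operated, the two definitions give the same probabilities.

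**Step 4, Interim analysis section read literally.** If a fraction g = qf of patients is never operated, the trigger is unmet when at least one of the first 10 is among them: 1 − (1−g)^10.

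- g = 0.05: 1 − 0.95^10 = 0.401
- g = 0.10: 1 − 0.90^10 = 0.651
- g = 0.20: 1 − 0.80^10 = 0.893

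**Step 5, delay under the monitoring section.** The expected number of patients needed for 10 completers is 10/(1−g). This is 12.5 at g = 0.2 and 20 at g = 0.5. At g = 0.5 the probability of at least 10 completers among all 20 patients is 0.588, so the look is not reached within the trial with probability 0.412.

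**The case against.** The strongest reply is that the monitoring section only points forward to the detailed description, so the Interim analysis section governs, and its set (the first 10 included) keeps never-operated patients. Each patient has two discharges, so the words in parentheses may only say which one is meant. The authors wrote rule 3 and presumably expected such patients in the look. This reading is plausible, but the text does not state it, and the pointer leads to a different set from the one named in the sentence containing it.

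The second reply is that the Medical Safety Officer follows safety continuously and all SAEs are reported to that officer and to the ethics committee. This stands as mitigation: a serious ISCON complication that prevented surgery would be reported by that route. It has no stated stopping threshold, however; the three rules are attached only to the interim look.

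Third, the rates used above are assumptions, and some are high. The Discussion reports no major ISCON complications in the cited meta-analysis and considers perforation unlikely. At q = 0.2 rule 3 would rarely be met under either definition. The literal block in step 4, by contrast, already matters at low rates.

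A reader might infer more than the documents support:

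- *Every stopping proportion is biased downward.* This is too broad. Rules 1 and 2 lose a patient only if the event rules out surgery for good, and late operations stay visible to rule 3.
- *All three rules concern the period before esophagectomy, so waiting for the second discharge serves no purpose.* Rule 2 is not limited to that period, so the later discharge can inform it.
- *The trigger can never be reached once a patient is not operated.* That follows from the literal reading only.
- *ISCON procedures should pause until the look is complete.* Nothing in reconciling the two sections requires this, and it is not part of this point.

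**Conclusion.** The point holds as a contradiction in a decision rule and is more than detail left to the full protocol: the article prints two sets of ten, and both triggers depend on an operation whose failure rule 3 is meant to count.

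The size depends on rates the documents do not give. At an assumed rule-3 rate of 0.5, the probability of meeting the rule is 0.62 with all of the first 10 kept. On 10 completers it falls to 0.21 when half of the rule-3 patients are never operated, and to 0 when all are. It is unchanged if all are eventually operated. These are illustrations under independence, not predictions for this trial.

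Because a benign reading exists and ongoing surveillance gives some protection, this is a should-fix point. The 40% thresholds themselves are not judged here.

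**What to change.** Reconcile the two sections with one definition:

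- **Set.** The first 10 patients in whom ISCON was started, all kept in the denominator of all three rules.
- **Trigger.** Hold the look once every one of the ten, and not only the tenth, has either been discharged after esophagectomy or is known not to have had esophagectomy within the protocol's own 30-day limit. Say also that a patient who dies before either point counts as resolved.
- **Rule 3.** Assess each patient without esophagectomy by that limit under rule 3, and count the patient if the reason is attributed to ISCON, as the rule already requires.
- **Five-patient SAE review.** Word its trigger in the same way: the first 5 patients in whom ISCON was started, each resolved as above.

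The cost is a change of wording in two sections. Sample size, thresholds and data collection stay as they are, and no pause in ISCON procedures is implied.
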